## Abstract

**Background:**

The aim of prehabilitation is to optimize patient specific modifiable risk factors before major surgery, in order to enhance the individual resilience. Due to the lack of universal guidelines, prehabilitation has been conducted in various ways, making it difficult to estimate its effect. In the Netherlands, proposed uniform prehabilitation protocols were developed. The aim of this study is to analyse clinical outcomes of prehabilitation when implemented as standard of care according to the proposed uniform protocols.

**Methods:**

Uniform prehabilitation protocols were created based on the multimodal program of the PREHAB randomized controlled trial. All hospitals in the Netherlands that implemented prehabilitation according to the proposed protocols, for patients undergoing elective colorectal surgery, will be asked to participate. This study will recruit 535 patients who underwent prehabilitation and 535 one‐to‐one nearest neighbour propensity score matched patients who did not undergo prehabilitation (historical cohort). Clinical outcomes will be compared between the prehabilitation group and the historical cohort group using regression analyses. The primary outcome of interest is 90‐day presence of postoperative complications. In addition, length of hospital stay and readmissions will be analysed.

**Discussion:**

Prehabilitation has been proven to reduce the risk of complications and hospital length of stay. Prehabilitation has however been defined in various ways, since there is no standardized program. This multicentre cohort study will estimate the clinical effect of prehabilitation implemented as standard of care according to proposed uniform protocols. Furthermore, the presented protocols can be used by other hospitals to set up a prehabilitation program.

Abbreviations1RMOne repetition maximum6CITSix‐Item Cognitive Impairment testCCIComprehensive Complication IndexCGAComprehensive geriatric assessmentCPETCardiopulmonary exercise testingCRCColorectal CancerDCRADutch ColoRectal AuditHADSHospital Anxiety and Depression ScaleHIITHigh‐intensity interval trainingHRmaxMaximum heart rateIQRInterquartile rangeiSWTIncremental shuttle walk testMETMetabolic equivalentsMMCMaxima Medical CentreNZaDutch health AuthoritiesPG‐SGAPatient Generated Subjective Global AssessmentRCTRandomised controlled trialSRTSteep Ramp TestVO2maxMaximal oxygen consumptionVSAQVeterans‐specific activity questionnaireWpeakPeak power output

## Background

1

Prehabilitation is designed to enhance a patient's physical condition prior to a major surgery, resulting in faster recovery and fewer complications. The fitter the patient is before surgery, the greater the chance of a better outcome [1, 2]. The prehabilitation program is tailored to the individual and includes physical training, customized nutrition, mental support, comorbidities (e.g. diabetes) and anaemia optimization, and smoking and alcohol cessation.

While it has been demonstrated that a patient's functional capacity can be improved through prehabilitation [3, 4] it is not yet clear to what extent prehabilitation actually improves surgical outcomes. Due to the lack of uniform guidelines, the prehabilitation program has been implemented in different forms. In some studies, aerobic exercise in combination with resistance training was offered as prehabilitation [5, 6, 7] while in another study only yoga was offered [8]. Several systematic reviews also found a lot of heterogeneity within prehabilitation studies [9, 10, 11]. This heterogeneity makes it difficult to compare results between studies and depicts the need to develop uniform guidelines.

With the international randomized controlled PREHAB study [12] the development of proposed uniform guidelines had begun. The protocol has for example been used as a blueprint for other studies. In the Netherlands, the Dutch Society of Surgery developed uniform prehabilitation protocols based on the international PREHAB RCT [12]. These proposed uniform protocols were assessed and adjusted by relevant scientific associations of sport medicine, anaesthesiology, surgery, internal medicine, geriatrics, medical psychology, physical therapy and nutritionists. Furthermore, anaemia screening and management was added. The proposed protocols were created to ensure the quality of prehabilitation programs in the Netherlands, to eventually evaluate outcomes of prehabilitation in a bigger population, and to evaluate the feasibility of implementing such a program. The proposed uniform protocols describe the core points of the prehabilitation program for patients with colorectal cancer (CRC). They can be used by other hospitals, inside and outside the Netherlands, to set up prehabilitation.

This paper describes the proposed uniform protocols created by the Dutch Society of Surgery and study protocol to evaluate its clinical effects. The study includes a nationwide multicentre study, which aims to evaluate clinical outcomes of prehabilitation when implemented as standard care, using the presented proposed uniform protocols. Also, length of stay and readmissions will be analysed.

## Methods

2

This nationwide multicentre observational cohort study will be conducted in several hospitals in the Netherlands that implemented the proposed uniform protocols and followed prehabilitation training facilitated by Maxima Medical Centre (MMC) and the foundation Fit4Surgery. Approval of the Medical Research Ethics Committee was requested but formal approval was deemed unnecessary, according to Dutch law (METC UMCG, 2022/079). The study procedure was approved by the Institutional Review Board of each participating hospital.

### Study Population

2.1

Adult patients undergoing elective colorectal resection for cancer and participating in the prehabilitation program are eligible for inclusion into the intervention cohort. Patients from the same hospital but from 2 years before implementation of the proposed uniform protocols, will be eligible for inclusion into the reference cohort. The intervention and reference cohort will be matched one‐to‐one based on propensity scores.

### Informed Consent and Data

2.2

All patients who underwent a prehabilitation program in one of the participating centres will be asked for informed consent. Based on local institutional review boards, patients will either be included upon providing written informed consent or upon applying the general opt‐out procedure. From every participating hospital, a historical cohort will be included to match with the prehabilitation group. The reference cohort will comprise patients from 2 years before when prehabilitation was not yet implemented in the respective hospital.

For both groups, data on patient characteristics, tumour and clinical outcome will be obtained from a nationwide quality registration database, the Dutch ColoRectal Audit (DCRA). The collected prehabilitation data will be combined with the DCRA data, based on date of birth, sex and operation date from the patient.

### The Prehabilitation Program

2.3

The prehabilitation program as described by the proposed uniform protocols includes the following five modalities.–Physical fitness–Nutritional status–Mental resilience–Comorbidity, anaemia, and frailty–Intoxications

The prehabilitation program should last at least 3–4 weeks to see an effect from the program. A longer prehabilitation period does not seem to have a negative effect on oncological treatment [13, 14]. If a patient can undergo surgery before the prehabilitation program is completed, it is preferable to complete the prehabilitation program first. Also after the surgery a healthy lifestyle is encouraged. A visit to a physiotherapist postoperatively (> 6 weeks) is preferred, where physical fitness measurements are repeated. Ideally, prehabilitation should be linked to rehabilitation, and these should be well integrated.

The flow chart in Appendix 1 shows the framework of screening, assessment, intervention, and re‐assessment for each modality in the prehabilitation program. Shared decision‐making is an integral part of all steps in the prehabilitation process.

### Interventions (According to the Proposed Uniform Protocols)

2.4

A more detailed overview of the interventions can be found in the appendices.Physical fitness (Appendix 2)Endurance training: Three times a week supervised high‐intensity interval training (HIIT) under the supervision of an (oncological) physiotherapist. Low‐intensity training at home on the other days. The training program is individualized and is based on the initial physical fitness assessment.Nutritional status (Appendix 3)Nutritional consultation with a dietitian: Aim for 1.2–1.5 g of protein per kg of body weight per day and energy intake according to calculated energy needs. Protein supplementation or medical nutrition can be used to achieve recommendations. Supplementation of vitamins and minerals is recommended.Mental resilience (Appendix 4)Providing information to the patient, taking into account the patient's health literacy, for example by a case manager.Psychological support: Consultation with case manager or specialized nurse. Referral to a medical psychologist in case of anxiety or depression.Comorbidity, anaemia, and frailty (Appendix 5 and 6)Blood sugar level: Measure HbA1c. Refer patients without diabetes with a threshold value > 42 mmol/mol (6%) to GP/internist. Refer patients with non‐insulin‐dependent diabetes with a threshold value > 53 mmol/mol to GP/diabetes nurse.Anaemia: Optimize haemoglobin levels if the value is < 8.0 mmol/L in men and < 7.5 mmol/L in women. Optimize iron deficiency preferably with intravenous treatment (Appendix 6).Frailty: Referral to a geriatrician in case of frailty based on, for example, the Groningen Frailty Indicator, G8 questionnaire, 6CIT questionnaire, and/or MiniCog or if a delirium has occurred previously.Intoxications (Appendix 7): Support for smoking cessation and cessation of other addictive substances.

### Study Outcomes

2.5

The primary outcome will be 90‐day postoperative complications. This will be graded according to Dindo et al. [15] and defined as presence or absence of any complication. Complications will also be scored with the Comprehensive Complication Index (CCI) [16]. A CCI > 20 will be labelled as a severe complication. Secondary outcomes will be length of hospital stay and readmissions.

Data on study outcomes is available in the DCRA database, which is a national mandatory audit. Prehabilitation data, for example start date of prehabilitation, number of training days, and outcomes of physical tests, will be collected separately and combined with the data from the DCRA.

### Statistical Analysis

2.6

A sample size calculation was made based on multiple logistic regression analysis for presence of post‐operative complications within the 90 postoperative days. Age, ASA score, Charlson Comorbidity score, BMI, type of surgery, and surgical approach will be considered as potential confounders. For the sample size calculation the effect size was based on the PREHAB study [12], with a two‐sided *p*‐value for significance of 0.05 and a desired power of 80%. To show a reduction in overall complication rate from 42.2% to 31.7% (odds ratio (OR) = 0.62) and being able to adjust for the above confounding factors, 535 patients are needed in each group, resulting in a total required study population of 1070 patients.

One‐on‐one propensity score matching will be performed to control for potential confounders. Propensity score matching will be achieved per hospital. Propensity scores will be calculated using multiple logistic regression analysis including, age, ASA score, Charlson Comorbidity score, BMI, type of surgery, and surgical approach as the independent variables and prehabilitation (yes/no) as the dependent variable. The resulting probabilities will be used to match each patient in the prehabilitation cohort with its nearest neighbour in the reference cohort. In case of multiple matches, a reference patient will be randomly selected. The effect of larger distances will be explored in sensitivity analyses.

Baseline characteristics and clinical outcomes will be presented for the prehabilitation and reference cohort. Continuous variables will be presented as mean (SD) and will be tested using the unpaired *t*‐test if there was a normal distribution based on the skewness and/or kurtosis value and presented as mean (SD). If a not normal distribution is nor present, the Mann–Whitney *U* test will be used and presented as median with interquartile range (IQR). Categorical variables will be presented as number per category with percentages and will be analysed using the Chi‐square or Fishers' exact test as appropriate. To calculate ORs and regression coefficients with 95%‐confidence intervals (95%CI), logistic and linear regression analyses will be used. Data will be analysed on an intention‐to‐treat basis. Per protocol analyses excluding patients who underwent insufficient prehabilitation will be done to explore the effect of prehabilitation compliance. The amount of missing data will be compared between the two study cohorts; baseline characteristics will be compared between patients with and without missing's to explore the possibility and direction of bias through missing's.

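### The planning odds ratio of 0.62 does not match the two rates beside it (they give 0.64), and 535 per group follows only from an unstated covariate inflation that is hard to square with a matched sample

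*Protocol article*

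**What the plan says.** All the planning figures stand in the Protocol article, 2.6 Statistical Analysis. The calculation is said to rest on multiple logistic regression for any complication within 90 days. The effect size comes from the earlier randomised PREHAB trial, at a two-sided 0.05 level and 80% power. The target is given as "To show a reduction in overall complication rate from 42.2% to 31.7% (odds ratio (OR) = 0.62"). Allowing for adjustment for six confounders, the text concludes that "535 patients are needed in each group, resulting in a total required study population of 1070 patients". The six are age, BMI, ASA class, Charlson index, operation type and surgical approach.

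The next paragraph of 2.6 adds one-to-one propensity score matching, which "will be performed to control for potential confounders". It is done within hospital, and the score is built from the same six variables. The Methods part of the abstract shows that the 535 + 535 are the matched patients: 535 who had prehabilitation and 535 matched historical patients.

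No R², variance inflation factor or attrition allowance is given.

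**The concern.** Two things do not fit.

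First, the odds ratio is printed in brackets as the odds ratio of the stated reduction, but the two rates do not produce it.

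Second, the rates, significance level and power give a requirement well below 535. The only bridge that the text offers is confounder adjustment. In the usual formula, that inflation depends on how strongly the exposure is related to the covariates in the analysed sample, and matching on those same covariates is meant to weaken that relation.

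At stake is how the result will be read. If the inflation applies, 535 per group has 80% power for the stated 10.5-point reduction. If matching makes it largely unnecessary, the same 535 has clearly more power for that reduction, or 80% power for a smaller one. A null result means different things in the two cases, and the article does not let the reader tell which was planned.

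**Working it through.** **Inputs** (all from 2.6): p1 = 0.422, p2 = 0.317, two-sided α = 0.05, power 80%, stated odds ratio 0.62, 535 per group, 1:1. R² is not in the document and is varied below as an assumption.

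**1. Odds ratio**

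- (0.317/0.683)/(0.422/0.578) = 0.4641/0.7301 = 0.636.
- Rounding of the rates allows only (0.3165/0.6835)/(0.4225/0.5775) = 0.633 to (0.3175/0.6825)/(0.4215/0.5785) = 0.638, so 0.62 is excluded.
- An odds ratio of 0.62 from 42.2% gives odds of 0.62 × 0.7301 = 0.4527, that is 0.4527/1.4527 = 31.2%.

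**2. Attempt to reproduce 535 without adjustment**

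n = [1.960 √(2 p̄(1−p̄)) + 0.842 √(p1(1−p1) + p2(1−p2))]² / (p1−p2)², with p̄ = 0.3695.

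- The terms are 1.960 × 0.6826 = 1.3379 and 0.842 × 0.6785 = 0.5711.
- n = (1.3379 + 0.5711)²/0.105² = 3.644/0.011025 = 330.5, so 331 per group.
- Other 80% versions: 328 (unpooled variance), 333 (Wald test on the log odds ratio), 331 (logistic regression formula with a balanced binary covariate), 350 (continuity correction).
- With an odds ratio of 0.62 (42.2% vs 31.2%): 299.
- At 90% power: 442. At 95% power: 547.

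No unadjusted 80% version gives 535. Using 0.62 widens the gap.

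**3. Inflation needed to reach 535**

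The standard allowance is n/(1−R²), where R² comes from regressing exposure on the covariates.

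- From 331: 535/331 = 1.62, so R² = 1 − 331/535 = 0.38.
- From 299: 535/299 = 1.79, so R² = 1 − 299/535 = 0.44.
- From 350: R² = 1 − 350/535 = 0.35.

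With R² = 0.38 the formula gives 331/0.62 = 534, so an adjustment of this size does restore the stated figure.

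**4. What such an R² means in a matched sample**

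For two equal groups, R² = d²/(d² + 4), where d is the standardised difference between the groups on the best linear combination of the covariates.

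- R² = 0.38 gives d = √(4 × 0.38/0.62) = 1.57 standard deviations.
- R² = 0.1 gives d = √(4 × 0.1/0.9) = 0.67 standard deviations, which is still poor balance.

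**5. Power of 535 per group for 42.2% vs 31.7%**

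Power = Φ[(0.105 √(535(1−R²)) − 1.3379)/0.6785]. At R² = 0 this is Φ[(2.4287 − 1.3379)/0.6785] = Φ(1.608) = 94.6%.

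| R² (assumed) | n per group for 80% | Power at 535 |
|---|---|---|
| 0 | 331 | 94.6% |
| 0.10 | 368 | 92.3% |
| 0.20 | 414 | 89.1% |
| 0.30 | 473 | 84.7% |
| 0.38 | 534 | 80.1% |
| 0.40 | 552 | 78.8% |

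At R² = 0, 535 per group has 80% power for about 8.3 points (42.2% to 33.9%, odds ratio (0.339/0.661)/0.7301 = 0.70).

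All of this treats the two groups as independent. Correlation within pairs and clustering by hospital are not modelled.

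**The case against.** A reader might infer that 535 is simply wrong, or that the study really has 95% power. The document does not support either. It says that the calculation was made for multiple logistic regression and that 535 leaves room for six confounders. The 331 is an unadjusted figure, so it does not use everything the text states, and 94.6% is only the R² = 0 case. An R² of about 0.38 brings back both 535 and 80%.

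An article may also leave the inflation factor to the full protocol or analysis plan, so its absence alone is no error. That stands. What remains is narrower: the only stated explanation for 535 needs a strong exposure–covariate relation in the very sample that matching is meant to balance.

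Matching may be imperfect. The plan takes the nearest neighbour within each hospital and leaves the effect of larger distances to sensitivity analyses. Residual imbalance is therefore possible, and an allowance for it is prudent. This makes the argument conditional but does not remove it, since about 0.38 would mean that matching had largely failed.

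On the odds ratio, 0.62 may be an adjusted estimate from the earlier trial. The text does not say so and prints it as the odds ratio of these two rates. The discrepancy is small (0.02, or about half a percentage point), and it gives no sign of underpowering: with 0.62 the unadjusted requirement is lower.

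**Conclusion.** The point holds in two parts of different strength.

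The odds ratio is certain. The rates give 0.64, and rounding cannot produce 0.62. The error is small, but it leaves the target effect stated in two incompatible ways.

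The sample size part is conditional. The 535 follows from the printed rates, level and power only with an inflation of about 1.6 (1.8 with 0.62), that is R² of about 0.38 to 0.44. This is hard to reconcile with pairs matched on the same six variables. If matching brings R² to between 0 and 0.1, power for the stated reduction is about 92% to 95% rather than 80%. These figures rest on the n/(1−R²) formula and on independent groups. The finding is that the basis of 535 is unexplained and in tension with the design. It does not show that the number is wrong or that the study is overpowered.

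**What to change.** In 2.6 Statistical Analysis:

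- **Odds ratio.** Change it to 0.64. If 0.62 was the intended target, change the second rate to 31.2% instead.
- **Sample size.** Either state the R² or inflation factor used and justify it for a sample matched on the same six variables, or give the power of 535 per group as conditional. For example: for 42.2% versus 31.7% at two-sided 0.05, 535 per group gives about 95% power if R² between prehabilitation and the covariates is 0, 92% at 0.1, 89% at 0.2 and 80% at 0.38, treating the groups as independent.

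Keep 535 per group. Do not add that the margin covers losses from matching: nothing in the article says so, and 535 is already the matched count.

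The cost is about two sentences of wording. No extra patients or data are needed.

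### The fixed six-variable propensity model leaves out sex and tumour characteristics such as clinical stage, although the registry supplies patient and tumour data for both cohorts

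*Protocol article*

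**What the plan says.** Under Statistical Analysis (2.6), the article states the covariates twice. For the sample size and the adjusted logistic regression: "Age, ASA score, Charlson Comorbidity score, BMI, type of surgery, and surgical approach will be considered as potential confounders". For the propensity model: "age, ASA score, Charlson Comorbidity score, BMI, type of surgery, and surgical approach as the independent variables". The lists are identical, neither is worded as a set of examples, and no rule is given for adding a variable. The purpose is explicit: one-to-one "propensity score matching will be performed to control for potential confounders", done within each hospital.

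Under Informed Consent and Data (2.2), for both groups, "data on patient characteristics, tumour and clinical outcome will be obtained from a nationwide quality registration database", namely the DCRA. The prehabilitation records are joined to it "based on date of birth, sex and operation date from the patient", so sex is held as well.

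The cohorts are formed differently. Under Study Population (2.1), adults having elective resection for colorectal cancer and "participating in the prehabilitation program are eligible for inclusion into the intervention cohort". For the comparison group, section 2.2 says: "The reference cohort will comprise patients from 2 years before when prehabilitation was not yet implemented in the respective hospital". Section 2.3 sets the programme at a minimum of 3–4 weeks and prefers that it be finished even when surgery could take place sooner.

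**The concern.** Matching balances what enters the score and whatever is correlated with it. Here the model is specified, and the specification leaves out variables of a kind that the study says it obtains. This is not a detail left to a fuller plan.

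The design gives a reason to expect imbalance in tumour variables. A patient enters the intervention cohort only by taking part in several weeks of preparation, and tumour stage or planned pre-treatment may influence who does so. Historical patients passed no such filter. If these factors also relate to postoperative complications, part of the observed difference would reflect who was selected and not what prehabilitation did. The direction is not known in advance.

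Sex is different. The article gives no reason why the sex ratio should shift between periods in the same hospital, so leaving it out costs mainly precision.

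**Working it through.** **1. Are the variables covered elsewhere?**

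| Variable | In the six-variable list? | Obtained? |
|---|---|---|
| Sex | No | Yes, linkage key (2.2) |
| Tumour location | In part, through type of surgery | Tumour data, both cohorts (2.2) |
| Clinical stage | No | Tumour data, both cohorts (2.2); item not named |
| Neoadjuvant treatment | No | Not stated |

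Section 2.6 also presents baseline characteristics by cohort, but states no step that takes an unbalanced variable into the score or the regression. The regression confounders are the same six, so regression after matching does not cover the gap.

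**2. The plan's own sample size.** Inputs from 2.6: 42.2% versus 31.7%, two-sided 5%, power 80%. The mean rate is 0.3695.

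n = [1.96·√(2·0.3695·0.6305) + 0.8416·√(0.422·0.578 + 0.317·0.683)]² / 0.105² = (1.338 + 0.571)² / 0.011025 ≈ 331 per group.

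The stated 535 is not reproduced without an allowance for covariates. From 331 it would need a squared multiple correlation of 1 − 331/535 ≈ 0.38, which the article does not give. This is an unstated input and not a proven error. The present point does not depend on it, except that the gap between 331 and 535 cannot be treated as spare patients.

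**3. What a given residual bias would do (illustration).** Assume no true effect and a 42.2% risk, with 535 per group.

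- Standard error of the difference = √(2·0.422·0.578/535) = 0.0302, or 3.02 points.
- Rejection probability = 1 − Φ(1.96 − b/3.02) + Φ(−1.96 − b/3.02), where b is the bias in points.
- b = 0: 5%.
- b = 1: b/3.02 = 0.33, giving about 6.3%.
- b = 2: b/3.02 = 0.66, giving about 10.2%.

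**4. What imbalance would produce such a bias (illustration).** Bias from one binary factor = imbalance × risk difference carried by the factor. Assume a factor present in 50% of the reference cohort, an overall risk of 42.2%, and no imbalance removed by the six matched variables.

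| Assumed odds ratio of factor | Risk difference | Bias at 5 / 10 / 15 points of imbalance | False-positive rate |
|---|---|---|---|
| 1.3 | 6.4 points | 0.3 / 0.6 / 1.0 points | 5.1% / 5.5% / 6.2% |
| 1.5 | 9.9 points | 0.5 / 1.0 / 1.5 points | 5.3% / 6.2% / 7.8% |
| 2.0 | 16.7 points | 0.8 / 1.7 / 2.5 points | 5.9% / 8.6% / 13.3% |

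Every odds ratio and imbalance here is an assumption; the article gives none. The planned difference is 42.2 − 31.7 = 10.5 points.

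**5. Room for more covariates.** At an assumed 10 prehabilitation patients per parameter, 535/10 gives about 53 parameters in a model pooled over hospitals. The number of hospitals is not stated, so the room within one hospital cannot be computed.

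**The case against.** Several objections are sound.

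- The propensity score is not the only protection. Matching is within hospital, the study concerns elective surgery, and adjustment in the regression is foreseen. These handle centre differences and gross urgency. They do not balance stage or pre-treatment among elective patients.
- Type of surgery and surgical approach carry some tumour information. This stands, and it means that the tables above overstate the bias to the extent that an omitted factor is correlated with the six matched variables.
- Section 2.2 says only that tumour data are obtained. It does not name stage or neoadjuvant treatment, so the availability of each item has to be confirmed.
- The baseline comparison would make imbalance in reported variables visible, and a condensed article may leave the response to the full plan. But the list printed here is closed and appears twice, so following it as written leaves these variables out.

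A reader might go further, add up several omitted factors acting in the same direction, and attribute a sizeable share of the planned 10.5-point effect to them. The article does not support that. It gives no imbalance, no association with complications, and nothing on direction; factors acting in opposite directions would partly cancel.

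**Conclusion.** The point stands as a weakness in the specified model that should be corrected. The article fixes six covariates, leaves out sex and clinical stage, and says that it obtains patient and tumour data for both cohorts. The one-sided participation filter makes imbalance in stage and pre-treatment plausible but does not demonstrate it. For sex, the argument is precision.

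The size is unknown. On the stated assumptions, a residual bias of 1 point takes the false-positive rate to about 6%, and 2 points to about 10%. A single factor in the range examined gives at most 2.5 points, well below 10.5. The omission therefore does not show that a difference of the planned size would be spurious. It is an avoidable source of doubt about a smaller difference or one near the significance threshold.

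**What to change.** In section 2.6, add clinical tumour stage, tumour location and sex to the propensity model and to the outcome regression after matching, together with neoadjuvant treatment where the DCRA extract holds it. Use clinical stage as recorded before prehabilitation or surgery, so that nothing adjusted for could be affected by the intervention. Confirm which items the extract contains for both cohorts, and fix the complete list before outcome data are linked, so that the choice cannot follow the results.

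The cost is mainly analysis wording, provided that the extract holds the items. The downside is that matching on more variables within a hospital may give slightly poorer or fewer matches. The plan should not count on a surplus in the 535 per group to absorb this: the article states 535 as the number needed with covariate adjustment and does not show how large that allowance is.

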## Appendix 2 Physical Fitness

### Definition and Goals

Major colorectal surgery can lead to substantial morbidity and mortality, particularly in elderly and patients with comorbidities. Low cardiorespiratory fitness has been found to be a major risk factor for complications after colorectal surgery [24]. Cardiorespiratory fitness is the maximum capacity of the body to take up oxygen and to transport it to the tissue [25]. It's expressed as VO2max (in mL/kg/min body weight) or metabolic equivalents (METs; where 1 MET is equal to the resting metabolism with an oxygen uptake (VO2) of about 3.5 mL/kg/min).

The goal is to make a preoperative risk assessment and to optimize the patient's cardiorespiratory fitness and muscle strength to reduce the risk of perioperative complications and to accelerate postoperative recovery of physical functioning.

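### The per-protocol analysis can exclude patients from the prehabilitation cohort only, so its result may reflect who complied and should not be read as the effect of compliance

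*Protocol article*

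**What the plan says.** Section 2.6 (Statistical Analysis) sets the main approach: "Data will be analysed on an intention‐to‐treat basis". The secondary analysis follows: "Per protocol analyses excluding patients who underwent insufficient prehabilitation will be done to explore the effect of prehabilitation compliance".

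The comparison is with historical controls. Section 2.1 says: "The intervention and reference cohort will be matched one‐to‐one based on propensity scores". Section 2.2 places the controls in the period "when prehabilitation was not yet implemented in the respective hospital". Section 2.6 will "match each patient in the prehabilitation cohort with its nearest neighbour in the reference cohort", within hospital, on a score built from "age, ASA score, Charlson Comorbidity score, BMI, type of surgery, and surgical approach as the independent variables".

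The article does not say what happens to the matched partner of an excluded patient, whether matching is repeated for the compliers, or whether the per-protocol model is adjusted.

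**The concern.** Insufficient prehabilitation can be observed only in patients who were offered prehabilitation. The rule therefore trims one cohort on something that happens after baseline and leaves no equivalent trimming in the other. If the trimmed patients have a different underlying risk, the remaining comparison mixes any programme effect with that difference.

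The article itself supplies a reason to expect a link. Appendix 2 says: "Low cardiorespiratory fitness has been found to be a major risk factor for complications after colorectal surgery". It also asks that training respect what the patient wants and is able to do. Neither fitness nor frailty is in the propensity score. An unmatched risk factor could thus drive both compliance and complications.

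At stake is the interpretation of a secondary result. The stated aim is to learn the effect of compliance. A per-protocol odds ratio further from 1 than the main one would invite the reading that more prehabilitation works better, when part or all of the gap could be selection.

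**Working it through.** **Benchmark.** Section 2.6 plans for 42.2% against 31.7%. These rates give (0.317/0.683)/(0.422/0.578) = 0.464/0.730 = 0.636; the article states 0.62. The article gives no figure for compliance or for the risk of non-compliers, so both are assumptions below.

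**Set-up.** Suppose prehabilitation has no effect and both full cohorts have a 42.2% risk. Let f be the share of treated patients excluded and R the complication odds ratio of non-compliers against compliers. The complier risk p solves

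(1 − f)·p + f·q = 0.422, with q = R·p/(1 − p + R·p).

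The apparent odds ratio, with all 535 controls kept and no adjustment, is [p/(1 − p)]/[0.422/0.578].

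**Worked case, f = 0.20, R = 2.** p = 0.3878 gives q = 0.7756/1.3878 = 0.5589. Check: 0.8 × 0.3878 + 0.2 × 0.5589 = 0.3102 + 0.1118 = 0.422. Apparent odds ratio = 0.6335/0.7301 = 0.87.

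**Chance of a falsely significant benefit in that case** (two-sided 0.05, so nominally 2.5% in the direction of benefit). The numbers are 535 × 0.8 = 428 treated and 535 controls. The pooled risk is 0.4068. The standard error is 0.03186 pooled and 0.03179 unpooled. The difference is 0.0342. Φ[(−1.96 × 0.03186 + 0.0342)/0.03179] = Φ(−0.89) = 19%.

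| f | R | Complier risk | Apparent OR | Chance of false significant benefit |
|---|---|---|---|---|
| any | 1 | 42.2% | 1.00 | 2.5% |
| 20% | 1.5 | 40.2% | 0.92 | 9% |
| 20% | 2 | 38.8% | 0.87 | 19% |
| 20% | 3 | 36.8% | 0.80 | 39% |
| 30% | 2 | 37.1% | 0.81 | 34% |
| 40% | 3 | 31.6% | 0.63 | 87% |

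The last row is an extreme case. It shows that the whole planned difference could in principle appear with no effect.

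**Reverse direction, f = 0.20, R = 0.5** (low-risk patients train too little). p = 0.4541 and q = 0.22705/0.77295 = 0.2937. Check: 0.8 × 0.4541 + 0.2 × 0.2937 = 0.422. Apparent odds ratio = (0.4541/0.5459)/0.7301 = 1.14, an apparent harm.

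**Does handling of the pairs settle it?** A simulation with a true odds ratio of 1.00 used one matched covariate and one unmatched risk factor, with 30% excluded:

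| Non-compliance depends on | Controls all kept | Controls kept, adjusted for matched covariate | Partners dropped |
|---|---|---|---|
| neither | 1.00 | 1.01 | 1.00 |
| matched covariate only | 0.93 | 1.00 | 0.99 |
| both | 0.88 | 0.92 | 0.93 |
| both, stronger dependence | 0.75 | 0.85 | 0.86 |

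Values of 0.99 to 1.01 are 1.00 within simulation error. Dropping partners, or adjusting for the matched covariate, removes the bias that runs through the matched covariate. Neither removes the part that runs through unmatched risk.

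**The case against.** The strongest reply is that the article does not commit the fault it might be charged with. A reader might infer that the rule necessarily breaks the matching and manufactures a benefit. The document does not support that. Loss of balance is certain only if the partners stay in. Section 2.6 is silent on this, and a condensed article may leave handling of pairs to a fuller plan. If the regression adjustment foreseen in section 2.6 is carried into this analysis, it also deals with imbalance in the six covariates.

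The direction of the bias is not established either. No data in the article show that excluded patients would be the frail or the sick. Appendix 2 directs supervised training especially at patients identified by the fitness thresholds and describes a programme suited to frail patients, so fitter patients might be the ones who do less. The sizes above follow from assumed inputs.

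A reader might also object that no cut-off for insufficient prehabilitation is given. Section 2.3 says "The prehabilitation program should last at least 3–4 weeks to see an effect from the program", but that is a programme recommendation and not an analysis definition. Sections 2.4 and Appendix 2 give session frequencies too. A missing cut-off is ordinary detail for an analysis plan and is not part of this point.

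Finally, the analysis is exploratory and the main result does not depend on it.

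All of this limits the point without removing it. The one-sided exclusion follows from the design, whatever a fuller plan says about pairs. Even with the favourable handling of pairs, bias from unmatched risk remains, and the stated purpose is still to explore an effect.

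**Conclusion.** The point holds in a conditional form. The exclusion acts on one cohort only, on behaviour after baseline, and the result is to be read as an effect of compliance. If poor compliers carry higher risk, an apparent benefit can appear with no true effect: about 0.92 to 0.80 for 20% excluded and a non-complier odds ratio of 1.5 to 3, before any adjustment. If compliance is unrelated to risk there is no bias, and if low-risk patients train less the sign reverses. The excluded share and the non-complier odds ratio are assumptions; only the 42.2% and the 535 come from the article.

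It would go too far to say that the per-protocol result will almost always look better, or that the study's main conclusion is compromised. The intention-to-treat analysis is unaffected. This is a matter to correct in a secondary analysis and in how it is described.

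**What to change.** State one of two routes for the per-protocol analysis.

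1. When a prehabilitation patient is excluded, remove the matched partner as well, or re-match the compliers within hospital. Adjust the model for the six matching covariates.
2. Keep all controls and weight the compliers by the inverse of their estimated probability of compliance, so that they represent the whole prehabilitation cohort. Estimate that probability within the prehabilitation cohort from the matching covariates and the baseline physical test. Section 2.5 already lists physical test outcomes among the data collected. Appendix 2 allows different tests, so the weighting model has to account for which one was used.

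Direct adjustment for fitness or frailty between cohorts should not be promised. Controls come from the national audit, and nothing in the article shows that these measures exist for them. The second route needs them only in treated patients, and it relies on the measured variables capturing what links compliance to risk.

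Under either route, describe the result as an association subject to selection and not as the effect of compliance.

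The cost is wording and some precision; no new data collection is needed. With 20% excluded, 428 pairs remain and confidence intervals under the first route widen by about √(535/428) = 1.12, or 12%. Keeping all controls gives √[(1/428 + 1/535)/(2/535)] = 1.06 before any loss from the weights. The per-protocol figure may also be less striking.
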